A few mobile EEG studies have investigated the electrocortical correlates associated with FOG in Timed Up-and-Go (TUG) tasks. They consistently found increased theta activity in right parietal and central brain regions during FOG episodes and during transition to FOG, suggesting an association of FOG with misguided integration of sensory information (Cao et al., 2021; Handojoseno et al., 2012, 2013; Shine et al., 2014). In addition, increased beta synchronization across the central cortex has been reported during FOG as well as an increase in beta activity across the parietal cortex along with changes in fronto-central beta coherence during transition to FOG (Handojoseno et al., 2015b; Shine et al., 2014). A surge in beta activation has been shown to be associated with motor symptoms in PD (Morelli and Summers, 2023) and is suggested to indicate impaired transmission of motor plans from frontal areas to the motor cortex (Shine et al., 2014). Additionally, investigating the differences between voluntary stopping and FOG, Cao et al. (2021) noted diminished power and different low-beta and delta power patterns in central regions during voluntary stopping compared to FOG (Cao et al., 2021). They also reported increased theta and alpha power over central and occipital regions during FOG compared to transition to FOG. Another study by Cockx et al. (2023) using fNIRS during walking showed a decrease in prefrontal cortex (PFC) activity during FOG compared to voluntary stopping (Cockx et al., 2024). Furthermore, they reported higher activation in the SMA and premotor cortex (PMC) in freezers compared to age-matched healthy controls during turning, stopping and walking through doorways. They emphasize the influence of the SMA in the pathophysiology of FOG and propose that FOG might emerge as a result of a disbalance between SMA and PFC. Moreover, connectivity analysis revealed increased coherence between central and frontal regions in the theta band during FOG, along with changes in theta synchronization during transition to FOG (Handojoseno et al., 2013; Shine et al., 2014). In this vein, Maidan et al. (2015) also reported an increased hemodynamic activation (fNIRS) in the frontal lobe before and during FOG (Maidan et al., 2015). However, these alterations were only observed in anticipated turns, indicating involvement of executive control mechanism in FOG; in line with the executive dysfunction hypothesis (Bardakan et al., 2022). Other important findings include intensified brain network synchronization with longer disease progression, which was consistently observed across various frequency bands (Asher et al., 2021). These results of increased coherence between frontal and central brain regions as well as increased network synchronization with increased disease severity potentially indicate the presence of compensatory neural mechanisms aimed at maintaining gait performance comparable to healthy controls (Poston et al., 2016).

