This research is motivated in particular by the limited evidence on the neural aspects of FOG and how effective countermeasures, such as vibrotactile cueing, can contribute to improvements of FOG related gait disturbances in everyday life. We will use a virtual walking scenario with automatic doorways to induce FOG to address three main research objectives. These objectives will focus on the neural mechanisms and pathways underlying FOG (RO1, RO2) and vibrotactile cueing (RO3). Our first research objective (RO1), aims to identify the cortical brain regions involved in FOG that show differential activation prior to the kinematic onset of FOG compared to normal, unimpaired walking. In the literature, the involvement of various brain regions such as frontal and central areas is reported (Asher et al., 2021; Cao et al., 2021; Handojoseno et al., 2015b; Shine et al., 2014). We expect involvement of similar brain regions (cf. perceptual dysfunction hypothesis (Bardakan et al., 2022)) in our virtual doorway scenario, but we also hypothesize differential activation based on the increased realism and environmental complexity achieved through the use of virtual reality. Second (RO2), we aim to delineate the neural signatures of induced FOG episodes, focusing on the temporal and frequency dynamics within the cortical areas of interest. Based on previous research we are expecting to see FOG specific changes in various frequency bands of interest, including alpha, beta and theta up to 5 s prior to FOG onset (Handojoseno et al., 2012, 2015b; Shine et al., 2014). To this end, we will compare FOG episodes vs. unimpaired walking through virtual doorways. Furthermore, we will analyze the connectivity of these dynamics across the brain regions involved. We expect to observe FOG-related changes in coherence, including increased theta coherence in fronto-central regions as reported previously (Shine et al., 2014).

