#### Statistical methods

2.8.4

To address our main research objectives, we will employ linear mixed effects models for our analyses. These models are well-suited for handling repeated measures and allow us to take advantage of the multi-trial data structure, while also accounting for both within-subject and between-subject variability. FOG episodes will be analyzed separately by motor context, distinguishing walking-FOG (forward locomotion, including doorway passage and straight walking) from turning-FOG (360° turning). Each FOG type will be compared against its corresponding unimpaired movement (Handojoseno et al., 2015a). The number of FOG episodes per type and participant will be reported.

First, we will identify cortical brain regions showing differential activation prior to the kinematic onset of FOG. Dependent variables include spatiotemporal characteristics of electrocortical and also hemodynamic brain activity that will be compared between FOG episodes and the corresponding period of unimpaired walking or turning. Second, we aim to delineate the neural signatures of FOG episodes, focusing on the temporal and frequency dynamics within the cortical areas of interest as defined by the first part of our analysis. This step includes analyzing the coherence of the neural dynamics across the brain regions involved. Lastly, we will examine if and how vibrotactile cueing may alter the neural signatures of FOG described above and whether it contributes to improved gait behavior when walking through virtual environments. This analysis will also focus on the reduction of the percentage time frozen, changes in kinematic and kinetic aspects of gait. All analyses will include relevant covariates, such as disease stage, motor symptom severity, prior experience with cueing and random effects accounting for inter-subject variability, and to investigate interindividual differences. To address the large number of comparisons across modalities, all analyses will include appropriate correction for multiple comparisons to control the rate of false-positive findings, using established methods such as Bonferroni correction or cluster-based permutation testing (Maris and Oostenveld, 2007).

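### RO2 takes its regions, including those for coherence, from the RO1 activation screen, so the fronto-central theta coherence hypothesis stated in advance may go untested or be tested only on regions chosen from the data

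*Protocol article*

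**What the plan says.** Section 2.8.4 (Statistical methods) sets an order of work. Step one: "First, we will identify cortical brain regions showing differential activation prior to the kinematic onset of FOG". The variables used there are both electrocortical and hemodynamic. Step two, on neural signatures, looks at behaviour over time and frequency "within the cortical areas of interest as defined by the first part of our analysis". The next sentence places connectivity in that step: "This step includes analyzing the coherence of the neural dynamics across the brain regions involved".

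The Introduction gives a meaning to regions being involved. RO1, it says, "aims to identify the cortical brain regions involved in FOG that show differential activation prior to the kinematic onset of FOG". For RO2 the Introduction also names a direction, a band and a pair of regions: "increased theta coherence in fronto-central regions as reported previously". That expectation carries no condition on what RO1 finds.

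Section 2.4 (Outcomes) lists spatial and temporal EEG changes in frequency bands as primary and does not name coherence. Section 2.8.4 requires correction for multiple comparisons, with Bonferroni and cluster-based permutation as examples. It gives neither a number of regions nor a division of the scalp.

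**The concern.** The hypothesis is about coupling between two regions, but the regions reach the analysis through a screen on activation within each region. These are different quantities: coupling may change with no activation difference on either side, and an activation difference need not bring a change in coupling. A screen on the wrong quantity can therefore remove the very pair that was named beforehand.

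At stake is whether a study that the Introduction calls confirmatory can answer one of its own stated expectations. If RO1 misses frontal or central areas, the article gives no rule for what happens to the test. If the analysts then pick a pair anyway, the choice is made after seeing the data. Because the Introduction frames the neural part of RO3 around the changes found in RO2, a gap in RO2 can carry forward to that part.

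**Working it through.** **1. Reading the sections together.** RO1 output = regions with differential activation (2.8.4 and Introduction). RO2 scope = areas defined by RO1 (2.8.4). Coherence = part of RO2, across the regions involved (2.8.4), a phrase that the Introduction attaches to the RO1 output. Hypothesis = fronto-central theta coherence, unconditional (Introduction). On the plain reading, a fixed hypothesis meets a data-driven choice of regions, with no fallback.

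**2. What can be computed.** The chance that both regions pass is not computable from the article: the number of regions, their division and the correction method are not fixed. The following illustrates scale only.

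Inputs from section 2.6: alpha 0.05, power 0.80, one tested predictor, five predictors in all, partial R² = 0.25, so f² = 0.25/0.75 = 1/3 (printed as 0.33). N = 30 is from the abstract.

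Power is from the noncentral F test for an R² increase, with 1 and N − 6 degrees of freedom and λ = f²N.

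- Check on the sample size: the smallest N with power of at least 0.80 is 27 (power 0.812 at f² = 0.33; 0.816 at 1/3). Section 2.6 states no N. The planned 30 exceeds 27, so it is sufficient on these inputs and is not in question.
- At N = 30: λ = 30/3 = 10 and df = 1 and 24. Power q per region is 0.858 at alpha 0.05, and 0.676 at 0.05/4 = 0.0125 (Bonferroni over an assumed 4 regions).

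If frontal and central are separate regions that both truly differ by the planned effect, both pass with probability q² (independent) up to q (fully dependent):

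| Screen | q | both, independent | both, fully dependent | at least one missed |
|---|---|---|---|---|
| Uncorrected | 0.858 | 0.74 | 0.86 | 0.14 to 0.26 |
| Bonferroni, 4 regions (assumed) | 0.676 | 0.46 | 0.68 | 0.32 to 0.54 |

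If coupling changes but activation in neither region does, the chance that both pass this one-test-per-region screen is at most alpha: 0.05 uncorrected, 0.0125 corrected.

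**3. How far the illustration moves.**

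- *Upwards, several bands.* With 4 regions × 3 bands (assumed), per-test power is 0.511 at 0.05/12. If each region has only one test that can carry it through, both pass with probability 0.511² = 0.26 (independent) to 0.51. If all three bands truly differ, independently, and any one suffices, each region passes with 1 − 0.489³ = 0.88, and both with 0.88² ≈ 0.78. The same correction thus gives 0.26 or 0.78, depending on an unstated selection rule.
- *Upwards, other routes.* Mixed models on repeated episodes and selection on hemodynamics could raise q.
- *Downwards.* A smaller effect lowers it. At f² = 0.25, q is 0.748 uncorrected and 0.525 over 4 regions, giving 0.56 and 0.28 for both regions if independent.

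**The case against.** The strongest reply is that the restriction is inferred. Section 2.8.4 describes a focus and never says that coherence is confined to RO1 areas. The coherence sentence does not repeat the RO1 definition, and nothing says that the hypothesis is dropped if a region fails. This stands as far as it goes: a reader might infer that the test will certainly not be run, and the article does not support that. It supports only that the test may not be run.

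A reader might also infer from the Introduction's EEG summary, "increased theta activity in right parietal and central brain regions during FOG episodes and during transition to FOG", that a faithful replication would leave frontal areas out. The documents do not support this either. RO1 covers several bands and hemodynamics, the Introduction reports frontal hemodynamic changes, its summary of earlier work names frontal and central regions, and RO1 expects similar ones. A frontal area could well be selected.

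Three further replies have weight. Coherence is not a listed outcome in section 2.4. A single fronto-central region could pass as one unit, in which case two separate passes are not needed. RO3 also rests on percentage time frozen and gait measures, which do not depend on RO2.

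Last, it can be said that electrode groups and fallback rules belong to a fuller plan. That would answer a complaint about missing detail. It does not answer this point, because the article states a rule for choosing RO2 regions, and that rule sits badly with a hypothesis in the same article. A plan that followed the rule would inherit the problem. Locating regions first is a legitimate design for exploration, but it does not suit a pair already named.

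**Conclusion.** The point holds in a limited form. As written, a coherence hypothesis stated in advance for a named pair of regions depends on a screen of a different quantity, with no safeguard. It may go untested, or be tested only on regions selected from the data.

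The size is not fixed by the article. The ranges of 0.74 to 0.86 (uncorrected) and 0.46 to 0.68 (Bonferroni over 4 regions) rest on these assumptions: frontal and central are separate units, both truly differ by the planned effect, each has one test, there is one observation per person in a regression, and N = 30. They show that selection of both cannot be taken for granted; they do not estimate a failure rate. The case that does not depend on these power figures is a change in coupling without a change in activation, where an activation screen offers the hypothesis almost no route to a test.

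Because coherence is not a listed outcome, this is a change worth making before analysis, not a threat to the study as a whole.

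**What to change.** In section 2.8.4:

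- Define a frontal and a central electrode group in advance, from the regions already named in the Introduction.
- State that theta coherence between these groups, FOG against the matching unimpaired movement, will be tested whatever RO1 shows, and include that test in the family corrected for multiplicity.
- Label coherence among other areas selected by RO1 as exploratory.

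This reconciles the Introduction with section 2.8.4. It needs a few sentences and no new data. The price is one more test in the corrected family, and so slightly stricter thresholds for the others.

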### Methods: monitoring

2.9

#### Data monitoring

2.9.1

No data monitoring committee is required as the measurements and interventions are conducted by qualified, impartial project employees. The employees also monitor participants for symptoms such as vertigo, confusion, pain, or any other symptoms during both the screening and familiarization on day one, and the walking tasks on day two. They are prepared to intervene if necessary.

#### Harms

2.9.2

For measurements on day 2, participants are required to refrain from taking medication for 12 h. That refrainment could exacerbate the symptoms of PD, similar to regular dose failures, and which may last until the day after. Physical and cognitive exhaustions of participants is monitored continuously between trials (cf. Participant timeline) and various safety measures are applied during testing (cf. Virtual Walking Scenarios). After the walking tests, participants are asked to take their usual medication and have a break.

#### Auditing

2.9.3

None.

## Discussion

3

With this study we aim to investigate the neural mechanisms and pathways underlying FOG (RO1, RO2) and the effects of vibrotactile cueing (RO3). To achieve this, we will examine the neurophysiological correlates of FOG using ambulatory EEG and fNIRS measurements in virtual walking environments. Participants will walk on a treadmill while immersed in these environments, allowing us to study the neurophysiological changes related to FOG episodes. In addition, a vibrotactile cueing device will be used aiming to improve FOG. Thus, we will compare cued versus non-cued walking and investigate its influence on the frequency of FOG episodes and the associated changes in brain activation. For RO1, we anticipate that our study will reveal distinct neurophysiological correlates of FOG in PD. Building on previous research that has identified key brain regions, such as the frontal and central areas (Asher et al., 2021; Cao et al., 2021; Handojoseno et al., 2015b; Shine et al., 2014), and various hypothetical neural mechanisms (e.g., executive dysfunction and interference model (Bardakan et al., 2022)) that seek to explain the pathophysiology of FOG, we expect to observe similar findings while also gaining additional insights through our novel and more ecologically valid experimental design. For RO2, we specifically expect to observe neurophysiological changes across various frequency bands of interest, including alpha, beta, and theta, occurring up to 5 s prior to the observable behavioral manifestations of FOG episodes when approaching virtual automatic doorways (Handojoseno et al., 2012, 2013, 2015b). For RO3, we hypothesize that vibrotactile cueing will reduce the occurrence of FOG episodes through mitigation of the neurophysiological changes linked to FOG (cf. RO2). Specifically, we expect that the neural signatures related to FOG will be less pronounced during cued walking compared to non-cued walking when approaching doorways.

By understanding the neural mechanisms underlying FOG episodes and the potential attenuating effects of vibrotactile cueing, we hope to contribute to the development of effective intervention methods for managing FOG in PD. The high temporal resolution of neurophysiological changes preceding FOG episodes may provide new insights about the timing of cueing devices to be effective and to potentially improving their efficacy. It might further give insights into how to design other appropriate intervention strategies, such as individualized cueing, to reduce FOG. Enhancing the effectiveness of cueing devices and developing alternative intervention strategies has the potential to refine the gait pattern in PD and thus improve patient mobility. This improvement in mobility can lead to more social interaction and therefore a better quality of life and psychological well-being (Lee and Choi, 2020). In addition, by facilitating a more stable gait, the number of falls in PD patients may be reduced, which in turn could lead to a reduction in hospitalization rates and associated healthcare costs.

## Ethics and dissemination

4

### Research ethics approval

4.1

This study was approved by the local Ethics Committee of the University of Münster, Faculty of Psychology and Sport and Exercise Sciences, Münster (protocol code: 2024-12-RS-Breaking the Freeze – Behavioral and Neural Aspects of Freezing of Gait and Vibrotactile Cueing in Parkinson’s Disease”; date of approval: 04.05.2024).

### Protocol amendments

4.2

Protocol amendments will be approved by the local Ethics Committee of the University of Münster, Faculty of Psychology and Sport and Exercise Sciences, Münster.

### Consent or assent

4.3

Members of the study team will introduce the study to the patients and provide all relevant information regarding the trial. Patients will receive an informed consent documentation, including a detailed overview of the study objectives, methods of data collection and data protection. Researchers will be available to answer any questions. Written informed consent will be obtained from all patients. The informed consent will also clearly state that participants can withdraw from the study at any time without any negative consequences.

### Confidentiality

4.4

Collected data will be pseudonymized, securely stored, and anonymized after data acquisition. Anonymized data will be stored for at least 10 years on password-protected servers to which only authorized researchers have access (cf. Data Management).

### Access to data

4.5

Access to anonymized data will be limited to authorized researchers directly involved in data acquisition and analysis. The data and code that support the findings of this study are available upon reasonable request from the corresponding author, [name]

### Ancillary and post-trial care

4.6

Participants must be accompanied by a healthy person, and both the participant and their companion are covered by a travel insurance policy for their journey to and from the laboratory.

### Dissemination policy

4.7

The findings of this study will be shared publicly through various channels: publication in peer-reviewed scientific journals related to the study’s topic, oral presentations at specialized conferences, regularly scheduled network meetings of Parkinson Münsterland +, and our social media channels and department homepage.
